**Table 3 Tab3:**
[figure not shown]
Study timeline

Primary outcomes include (i) PA drop-out ratio; (ii) PA levels; (iii) metabolic and health outcomes (HbA1c, blood pressure, waist circumference and BMI); and (iv) quality of life (SF-12) (see Table 4).

**Table 4 Tab4:** Overview of outcomes, outcome measures, instruments and assessment time points

Outcomes	Outcome measures	Instrument/who measures	Assessment time point
Personal information	Age, gender, civil status, living arrangement, educational background, medical conditions, smoking and alcohol habits.	Primary care records/self-report	T0
Primary clinical trial outcomes			
●Physical activity	Daily counts per minute and intensity of exercise, and daily step counts.	ActivPal®/research team	T0, T1, T2, T3
●Physical activity drop-out ratio	Less of 80% of attendance during the intervention or auto-reported drop out after intervention (yes/no)	Excel/research team	T0, T1, T2, T3
●Quality of life	Physical function, physic role, corporal pain, general health, vitality, social function, emotional role and mental health	SF-12 questionnaire/research team	T0, T1, T2, T3
●Blood pressure	Systolic and diastolic blood pressure; heart rate	OMRON M6 comfort/nurse	T0, T1, T2, T3
●Blood glucose levels (last 3 months)	HbA1c	CATSALUT Dataset	T0, T1, T2, T3
●Anthropometry	Waist circumference and BMI	Measuring tape and coefficient between weight and height/nurse	T0, T1, T2, T3
Secondary clinical trial outcomes			
●Socioeconomic status	Job, education and income	Job and education level and individual and family annual income/research team	T0
●Social network index	Number of social interactions with family friends or mates	Berkman et al. [47] questionnaire with adaptations [48]/research team	T0
●Demographic and background information	Sex, gender, age, ethnic origin, marital and family status or obligations and medication	Self-report information/nurse	T0, T1, T2, T3 (only apply times for medication)
Primary qualitative study outcomes			
●HCP and T2DM perspective on the intervention	Perceptions and experience to examine the feasibility about the intervention and applicability to everyday life	Focus groups /research team	T1

Assessment time points: T0 = baseline pre-intervention, T1 = at month three of intervention, T2 = at month 12 (9 months after the end of the intervention), T3 = at month 24 (21 months after the end of the intervention). *HCP*, health care professionals; *T2DM*, type 2 diabetes mellitus

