### PA drop-out ratio

During the intervention, dropout will be considered as less than 85% attendance of scheduled sessions [50].

After the intervention, PA dropout will be measured by asking the participants if they continue to undertake any kind of PA in their daily life. The answer will be registered as yes or no, and it will be noted what kind of PA is done. Participants will be asked once a month until the 21-month post-intervention follow-up through telephone calls and messages. In addition, the SBPAAT screening tool will be used to register whether participants are active or inactive at the follow-ups (*T* = 1, 2 and 3).

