### Data analysis

Descriptive statistics will be reported as the mean and standard deviation (SD) for quantitative variables (PA and metabolic and health assessment outcomes) and using frequency rates and percentages for qualitative variables (drop-out ratio, medication, quality of life, socioeconomic status and social network). The Shapiro–Wilk test will be used to assess the normality of quantitative variables. For each outcome variable considered, the effect of the three different interventions will be assessed by a two-factor analysis of variance: the first factor will be the treatment group and the second factor will be time. To determine whether one treatment improves the scores of the study variables compared with the other, two-factor ANOVA tests will be performed with linear mixed models for repeated measures. An odds ratio and hazard ratio will be performed comparing drop outs in SENWI, NW and the control group at 3, 9 and 21 months.

Socioeconomic status and social network index will be analysed and compared in relation to the PA attendance at 3, 9 and 21 months post-intervention using the non-parametric chi-square test (*χ*^2^) and logistic regression when appropriate.

Demographic and other patient characteristics recorded (e.g. age, gender, marital status, income, education and employment) will be tabulated and analysed as covariables alongside the PA levels and PA drop-out ratio at the beginning and at 21 months post-intervention. Correlations and differences between groups and these variables will be analysed. Difference in baseline levels of outcome variables (PA, drop out, HbA1c and so forth) will be identified, and the correlation with the different covariables will be assessed.

A *p*-value of < 0.05 will be considered statistically significant. When multiple comparisons are carried out, the Bonferroni correction will be applied. All analyses will be carried out with the obtained data without employing missing data replacement techniques. Analysis will follow intention-to-treat principles. Assumptions will be tested regarding missing data, randomization and contamination. All analyses will be carried out using the R version 3.6.1 software.

The individual intervention will be regarded as successful if (i) it leads to an average increase in activity and (ii) the participant did not drop out of the PA (NW or any kind of PA) in the long run (i.e. if the patients answer yes when asked if they still do PA of some kind).

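### Participants who cannot be reached at 9 and 21 months leave the drop-out odds ratio, although the plan claims intention-to-treat and drop-out is a primary outcome

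*Protocol article*

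**What the plan says.** The Data analysis section of the protocol article sets one missing-data rule for everything: "All analyses will be carried out with the obtained data without employing missing data replacement techniques". The next sentence reads "Analysis will follow intention-to-treat principles". The one after adds "Assumptions will be tested regarding missing data, randomization and contamination", without naming a test or saying what would follow from it.

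PA drop-out is listed first among the primary outcomes. Its planned comparison is: "An odds ratio and hazard ratio will be performed comparing drop outs in SENWI, NW and the control group at 3, 9 and 21 months". Its definition has two parts:

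- **During the intervention** it is set by session attendance: "During the intervention, dropout will be considered as less than 85% attendance of scheduled sessions". Table 4 gives a different threshold: "Less of 80% of attendance during the intervention or auto-reported drop out after intervention (yes/no". That mismatch is a separate matter that also needs reconciling.
- **After the intervention** it is a yes/no answer on whether the participant still does any PA. The section PA drop-out ratio says: "Participants will be asked once a month until the 21-month post-intervention follow-up through telephone calls and messages".

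For continuous outcomes, "two-factor ANOVA tests will be performed with linear mixed models for repeated measures".

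Nothing in the article says how a participant who cannot be reached is classified for drop-out.

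**The concern.** For an outcome that exists only when the participant answers, using obtained data only and analysing everyone as randomised cannot both be done. The unreached participant has no obtained value, so the odds ratio at 9 and 21 months is computed among responders. Someone who no longer answers calls about PA is plausibly more likely to have stopped PA. Non-response would then depend on the outcome itself.

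The promise to test assumptions does not repair this. Whether data are missing at random cannot be established from the observed data, and no action is tied to the test.

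The article also points to three different treatments of a non-answerer:

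| Source | What happens to a participant who does not answer |
|---|---|
| Success criterion, Data analysis (the patient must answer yes) | Not a success |
| Table 4 (drop-out must be self-reported) | Not a drop-out |
| Obtained-data rule, Data analysis | Excluded |

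Drop-out is the trial's headline outcome, and the article says that the 9- and 21-month comparisons are needed to judge whether the socio-ecological Nordic walking programme (SENWI) works. A choice left open here could be made after the data are seen, and it can change the answer.

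**Working it through.** **Inputs from the article.** There are 48 participants per arm and 144 in total, with 15% expected drop-out of participants (Sample size). The Background cites drop-out of 20–50% within 3–6 months, and the Discussion cites long-run non-adherence above 40%. The article gives no non-response figures by arm or by activity status, so those below are assumptions.

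**Number exposed.** If the 15% is read as loss to contact, 144 × 0.15 = 21.6, so about 22 participants leave the analysis. That leaves 48 × 0.85 = 40.8, about 41 per arm.

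**Formula.** Let p be the true drop-out proportion, m_d the share of drop-outs not reached and m_a the share of adherers not reached.

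- Observed proportion = p(1 − m_d) / [p(1 − m_d) + (1 − p)(1 − m_a)]
- Observed odds = true odds × k, where k = (1 − m_d)/(1 − m_a)
- Observed odds ratio = true odds ratio × (k in one arm / k in the other)

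The odds ratio is therefore unbiased exactly when k, the ratio of response among drop-outs to response among adherers, is the same in both arms.

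**Illustration 1: no true difference.** Assume p = 0.40 in both arms and m_a = 0.05, so observed adherers are 0.60 × 0.95 = 0.57.

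| Assumed m_d | Observed drop-outs | Observed proportion | Total missing |
|---|---|---|---|
| 0.50 | 0.40 × 0.50 = 0.20 | 0.20/0.77 = 26.0% | 23% |
| 0.20 | 0.40 × 0.80 = 0.32 | 0.32/0.89 = 36.0% | 11% |
| 0.30 | 0.40 × 0.70 = 0.28 | 0.28/0.85 = 32.9% | 15% |

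- The first row against the second gives an odds ratio of (0.20/0.57)/(0.32/0.57) = 0.625, or 1/0.625 = 1.6 with the arms reversed. The truth is 1.0.
- The third row in both arms leaves the odds ratio at 1.0 but reports 33% instead of 40%.

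**Illustration 2: equal total loss is not a safeguard.** Assume true drop-out of 50% in control and 30% in SENWI. The true odds ratio is (0.30/0.70)/(0.50/0.50) = 0.43. Let 15% be missing in each arm, all of them drop-outs.

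- Control: (0.50 − 0.15)/0.85 = 41%
- SENWI: (0.30 − 0.15)/0.85 = 18%
- Odds ratio = (0.15/0.70)/(0.35/0.50) = 0.31

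If instead the same share of drop-outs (30%) is missing in each arm, the proportions are 0.35/0.85 = 41% and 0.21/0.91 = 23%. The odds ratio is then (0.21/0.70)/(0.35/0.50) = 0.43, unchanged.

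**Effect of counting the unreached as dropped out.** In the first two rows of illustration 1, the arms become 0.20 + 0.23 = 43% and 0.32 + 0.11 = 43%. The odds ratio is 1.0 and drop-out is overstated by 3 points. This exact recovery relies on adherers being equally reachable in both arms (5% unreached in each).

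**The case against.** Several points on the other side stand, and they limit the finding.

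- **Continuous outcomes.** A reader might infer that the plan handles no missing data at all and that its intention-to-treat claim fails throughout. It does not. A linear mixed model uses incomplete series and is valid under missing at random without imputation. HbA1c comes from the health-system dataset and does not depend on answering calls.
- **Month 3.** A reader might infer that the 3-month odds ratio also loses its drop-outs. In the two walking arms, a participant who disappears fails the attendance threshold and is counted. Only controls, who have no scheduled sessions, lack such a record.
- **Hazard ratio.** It is not a complete-case analysis. Monthly contact keeps each person at risk until last contact, so the problem there is informative censoring.
- **Chi-square and logistic tests.** These relate socioeconomic status and social network to attendance. They are not the treatment comparison.
- **Differing contact by arm.** A reader might infer that weekly physiotherapist contact in two arms makes unequal loss likely. That contact runs only during the intervention. Afterwards the article describes the same monthly calls for participants, with no distinction by arm.
- **Assumed figures.** The non-response rates are invented for illustration. The 0.63 comes wholly from the assumed difference between arms.

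These points do not remove the gap at 9 and 21 months. It also cannot be treated as detail left to an analysis plan, because the article itself fixes the obtained-data rule and applies it to all analyses.

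**Conclusion.** The concern holds for self-reported PA drop-out at the 9- and 21-month follow-ups, and for controls at month 3. There, the obtained-data rule removes unreached randomised participants from a primary outcome while the plan claims intention-to-treat.

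Drop-out is probably understated, on the plausible but undocumented assumption that unreached participants have more often stopped PA. Bias in the odds ratio is possible, not established. It requires the ratio of response among drop-outs to response among adherers to differ by arm, and equal total loss does not rule that out. Under the assumed figures, a true odds ratio of 1.0 becomes 0.63 or 1.6, and one of 0.43 becomes 0.31. With the same ratio in both arms only the level is wrong (33% for 40%).

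The documents do not support the view that the whole analysis is complete-case, or that a bias in a known direction should be expected. This should be corrected before analysis.

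**What to change.** Amend the Data analysis section as follows:

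1. Exempt the drop-out outcome from the obtained-data sentence.
2. Keep all randomised participants in the drop-out denominator, in the arm to which they were randomised.
3. In the main analysis, count participants unreached at the 9- or 21-month follow-up as dropped out, and likewise controls unreached at month 3. State what counts as unreached.
4. Add multiple-imputation and best/worst-case sensitivity analyses. For the hazard ratio, vary the assumption about participants censored at last contact.
5. Reconcile the success criterion with Table 4, so that a non-answerer has one classification throughout.
6. State that the linear mixed model with all available data is the analysis of continuous outcomes. The Abstract lists a two-factor analysis of variance and then the mixed-model version, which leaves it unclear whether a separate plain ANOVA is meant.

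The cost is wording and a few extra runs. Reported drop-out will be slightly higher. Counting the unreached as dropped out is itself an untestable assumption, and the sensitivity analyses are there to probe it.

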### Participants

A total of 144 participants (randomized in two intervention groups and one control group) will be included in this study. The study will be conducted in the Central Catalonia health area (Spain). Participants will be recruited from Monistrol de Montserrat *Primary Care Center* (CAP), Vic Sud CAP (Vic), CAP les Bases (Manresa), Hospital *Sant Bernabé* (Berga) and Anoia CAP (Igualada).

Inclusion criteria for eligibility will include participants (i) with T2DM, (ii) that have no major physical limitations prescribed by the doctor or any HCP and (iii) that are physically inactive according to the Spanish version of a Brief Physical Activity Assessment Tool – SBPAAT screening tool [44]. Participants will be excluded if they (i) are pregnant or have T2DM due to gestation; (ii) are unable to freely consent to take part in the study; (iii) are unable to understand the study materials or PA intervention; (iv) have complications such as neuropathy, retinopathy and nephropathy; (v) have relative or absolute contraindications to do PA; and (vi) have a body mass index over 34.9 kg/m^2^ since Nordic walking uses poles that require free arm mobility that is impaired by a body mass index over 35 kg/m^2^.

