### Sample size

We calculated the sample size (*n* = 144) in relation to the drop-out ratio in PA interventions showed by other studies (15%) [45] with a balanced one-way analysis of variance power calculation of 80%, a significance level of 5%, an expected drop-out rate in participants of 15% and an effect size of 0.5. As a result, 48 participants will be needed in each group in the three-arm randomized controlled trial.

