### Study interventions

A three-arm randomized controlled trial will assess the impact of a primary care-based PA intervention implementing SENWI against an isolated NW programme (comparison group 1) (see Fig. 1) and usual PA advice (e.g. to walk) provided by HCPs (comparison group 2).

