The SENWI programme will be regarded as improving usual healthcare if it increases PA at any level [2]. We will assess changes between groups in indicators relating to people living with T2DM health issues including HbA1c, weight, waist circumference and blood pressure. Finally, comparison between groups variables at 9 and 21 months will be needed to see whether the SENWI protocol is effective or not, and to determine if the PA drop-out ratio increases after removing the social and economic support (i.e. study intervention), in relation to the NW and SENWI.

To establish how the intervention works and for whom moderator and mediator analysis will be conducted. Suspected moderators will include participants’ demographic factors (e.g. socioeconomic status) and baseline intentions to engage in activity (e.g. sociocultural needs).

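### The rule for declaring SENWI better than usual care is not tied to the planned between-group test, so the plan holds two success criteria that can disagree

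*Protocol article*

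**What the plan says.** All the relevant statements stand in the protocol article, most of them under Data analysis.

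- **Programme-level rule:** "The SENWI programme will be regarded as improving usual healthcare if it increases PA at any level". It gives no measure, time point, minimum change, contrast, test or interval.
- **Rule for the individual intervention:** this has two parts. The first is that "it leads to an average increase in activity". The second, joined to it by an and, is that the participant is still doing some kind of activity in the long run, by self-report.
- **Effectiveness statement, in the same paragraph as the programme-level rule:** "comparison between groups variables at 9 and 21 months will be needed to see whether the SENWI protocol is effective or not".
- **Planned analysis:** two-factor (group and time) mixed models, introduced with the words "To determine whether one treatment improves the scores of the study variables compared with the other". A p-value below 0.05 counts as significant, and Bonferroni applies when several comparisons are made.

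Three other places bear on how the rule would behave. Under Participants, the trial enrols people "that are physically inactive according to the Spanish version of a Brief Physical Activity Assessment Tool". Under Study procedure, controls are to be told to increase their activity as well. Under PA assessment and in Table 4, the activPAL supplies several measures (among them MVPA, light activity, standing and steps), each taken at baseline and at three follow-ups.

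**The concern.** The sentence that says when SENWI will be held to improve on usual care is the one a reader will use to judge the trial's main claim. As written it can be met by a rise of any size, and it does not say whether the rise is measured against control or against SENWI's own baseline.

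This matters in this population. Entrants are selected for inactivity and controls are also told to be more active, so activity could rise in every arm without any effect of SENWI. If the rule is then read as a within-arm change, the claim of improving on usual care could be made when usual care improved just as much. The planned mixed model would show no difference, and the protocol does not say which of the two statements decides.

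**Working it through.** The protocol gives no false-success rate for its rule, so there is no stated figure to reproduce. The check compares how often each criterion declares success when SENWI has no effect.

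**Inputs from the protocol (Sample size).** 48 per arm, with "a significance level of 5%, an expected drop-out rate in participants of 15% and an effect size of 0.5". Evaluable per arm: 48 × (1 − 0.15) = 40.8, taken as 41. Sidedness is not stated; two-sided is assumed.

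**Inputs assumed.** Normally distributed mean changes; an upward drift of 0.1 to 0.2 SD common to all arms; a baseline/follow-up correlation r of 0.5 to 0.7. The protocol gives none of these.

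**Step 1. Literal rule, no effect, no drift.** The estimated change, or the estimated difference from control, is symmetric about zero. So P(estimate > 0) = Φ(0) = 0.50. This holds on either reading, within-arm or as a point estimate against control.

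**Step 2. Within-arm reading, shared drift s (in SD units of the measure).** The SD of the change is √(2(1 − r)), so

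P(mean change > 0) = Φ( s√n / √(2(1 − r)) ), with √41 = 6.403.

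| s | r | argument of Φ | P(success) |
|---|---|---|---|
| 0.1 | 0.5 | 0.640 / 1.000 = 0.640 | 0.74 |
| 0.1 | 0.7 | 0.640 / 0.775 = 0.827 | 0.80 |
| 0.2 | 0.5 | 1.281 / 1.000 = 1.281 | 0.90 |
| 0.2 | 0.7 | 1.281 / 0.775 = 1.653 | 0.95 |

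**Step 3. Adding a significance test within the arm.** At s = 0.2 and r = 0.5, P = Φ(1.281 − 1.96) = Φ(−0.679) = 0.25. A p-value alone does not repair the rule if the contrast is still within-arm.

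**Step 4. The planned between-group test.** For one measure at one time, two-sided 5%, the chance of a significant difference in SENWI's favour is 0.05 / 2 = 0.025. With Bonferroni over the three pairwise comparisons of arms it is 0.05 / (3 × 2) = 0.0083. A drift shared by all arms cancels in the difference, so these figures do not change with s.

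**Step 5. The two criteria together.** Suppose SENWI and control both rise by 0.2 SD. The success sentence, read within-arm, is met with probability 0.90 to 0.95. The planned test favours SENWI with probability 0.025. The protocol allows both conclusions from the same data.

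**The case against.** The strongest reply is that the plan already contains what the sentence lacks. The Data analysis section sets out mixed models comparing the treatments, a significance threshold, a Bonferroni correction, and odds and hazard ratios for drop-out across the arms. The paragraph with the success sentence goes on to say that a between-group comparison is needed to judge effectiveness. The sentence also speaks of improving usual healthcare, and usual advice is a randomised arm, so a comparative reading is natural.

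Much of this stands, and it rules out two stronger readings that a reader might infer.

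- **That the plan has no comparison with control and no error control.** The documents contradict this. Both exist; what is missing is the link to the success sentence.
- **That an ineffective programme would usually be declared a success.** The base case is 50%. Going above it needs one of two things. The first is the within-arm reading plus a drift whose size the protocol does not give: entry is by a brief screening tool and the outcome by activPAL, and no correlation between them is stated. The second is taking the phrase about any level to mean any one of several measures, for example 69% to 94% for any of four at assumed correlations of 0.8 down to 0. The text does not say that; level may equally mean amount or intensity.

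Nor does the rule for the individual intervention show that a rise alone suffices, since it also requires continued activity.

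The reply does not remove the defect. Even on the comparative reading, the sentence asks only for an increase of any size, which a point estimate meets half the time under no effect. The effectiveness statement names neither a measure nor which of its two follow-ups decides.

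**Conclusion.** The concern holds as a failure to connect the success rule to the planned test. This is a rule that the protocol states and fixes badly, not a detail left for a statistical analysis plan.

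The 50% figure needs only symmetry of the estimate under no effect. The range of 74% to 95% is conditional on the within-arm reading, 41 evaluable per arm, and the assumed drift and correlation; it shows what the wording permits and does not predict this trial's result. The contrasting 2.5% assumes a two-sided 5% test on one measure at one time.

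**What to change.** Restate the programme-level rule along these lines: SENWI will be regarded as improving on usual care only if the SENWI-minus-control difference from the planned mixed model, on one pre-named activPAL measure at one pre-named follow-up, favours SENWI and its Bonferroni-adjusted confidence interval excludes zero. The sponsor should choose the measure and time; daily MVPA at T3 is one workable example. State which comparisons the Bonferroni correction covers. Report the success definition for the individual intervention descriptively, by arm.

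This does not require demoting any of the other listed primary outcomes. Only wording changes: no new data, visits or participants are needed. The price is that success becomes harder to declare. The sponsor should also know that the Sample size section states power for a one-way analysis of variance and not for this adjusted contrast.

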### Quantitative and qualitative outcomes

Quantitative assessments will be conducted by researchers at the following time points: T0 = baseline preintervention, T1 = at month three when the intervention has finished (post-intervention), T2 = at month twelve (9-month follow-up) and T3= at month 24 (21-month follow-up) (Table 3 shows the SPIRIT table). All researchers in charge of conducting the assessments will take a standardized training session.

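### Whether drop-out rises once support ends is judged on a ratio whose definition changes at that same moment, so a T1-to-T2/T3 change mixes removal of support with a change of measure

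*Protocol article*

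**What the plan says.** The PA drop-out ratio is listed first among the primary outcomes. The section on it gives two definitions. While the programme runs: "During the intervention, dropout will be considered as less than 85% attendance of scheduled sessions". Once it is over: "After the intervention, PA dropout will be measured by asking the participants if they continue to undertake any kind of PA in their daily life". Table 4 makes the same switch in one line, with a different threshold: "Less of 80% of attendance during the intervention or auto-reported drop out after intervention (yes/no".

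The switch falls at the end of the programme, which the outcomes section places at "T1 = at month three when the intervention has finished (post-intervention". That is also when support is withdrawn.

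The Data analysis section treats drop-out as one outcome over time: "An odds ratio and hazard ratio will be performed comparing drop outs in SENWI, NW and the control group at 3, 9 and 21 months". Its long-run success criterion confirms how lenient the later rule is: a participant has not dropped out "if the patients answer yes when asked if they still do PA of some kind". The section then sets the question at issue here, "to determine if the PA drop-out ratio increases after removing the social and economic support (i.e. study intervention), in relation to the NW and SENWI".

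The drop-out section adds that "the SBPAAT screening tool will be used to register whether participants are active or inactive at the follow-ups", meaning T1, T2 and T3. Table 4 schedules activPAL at T0 to T3. Neither measure is named for the question about removing support.

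**The concern.** To ask whether a ratio increases after something is removed, one needs a value from before the removal. For drop-out the only such value is session attendance up to month 3. Every later value is an answer about any kind of PA. The two rules differ greatly in strictness: one needs 80% or 85% attendance at supervised sessions, the other only some activity of some sort. Because the rule and the support change together, a before-after difference in this ratio cannot be attributed to either one.

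This matters because keeping people active after the programme ends is the rationale of the trial. If the ratio falls after month 3 because the bar was lowered, the trial could conclude that gains survive the withdrawal of support when some participants have in fact relapsed.

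**Working it through.** The plan gives no figure for this comparison, so there is none to reproduce. The point does not depend on the sample size.

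**Inputs**
- D1, the share counted as drop-outs by attendance at T1. The document does not predict it. The Background cites drop-out of 20–50% in the first 3–6 months of earlier programmes; I use that range as a proxy.
- q, the share of those poor attenders who still do some PA and so answer yes later. Not in the document; full range 0 to 1.
- r, the share of good attenders who later stop all PA. Not in the document; r = 0 means that no good attender stops.

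**Reading 1: status at each visit (drop-out section)**

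Later ratio: D2 = D1(1 − q) + (1 − D1)r.

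Change: D2 − D1 = (1 − D1)r − D1·q.

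The first term is real relapse among good attenders. The second comes from the change of definition alone and is never positive. With behaviour unchanged (r = 0), D2 = D1(1 − q):

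| D1 | q = 0 | q = 0.5 | q = 0.75 | q = 1 |
|---|---|---|---|---|
| 20% | 20% | 10% | 5% | 0% |
| 50% | 50% | 25% | 12.5% | 0% |

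For the ratio merely to stay level, r must equal D1·q/(1 − D1). At q = 0.5 this is 0.20 × 0.5/0.80 = 12.5% when D1 = 20%, and 0.50 × 0.5/0.50 = 50% when D1 = 50%. Relapse among good attenders below that level would appear as a fall.

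**How easily an active person meets the attendance rule for drop-out**

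Take someone who attends each session independently with probability 0.85 and stays active throughout. The chance of falling below the threshold is binomial:

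| Sessions | 85% rule | 80% rule |
|---|---|---|
| 24 (two a week for 12 weeks) | 0.50 | 0.29 |
| 26 (total stated for each group) | 0.56 | 0.19 |

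After month 3 the same person answers yes and is not a drop-out.

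**Reading 2: ever dropped out (the *or* in Table 4, carried forward)**

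D2 = D1 + (1 − D1)r. This can only stay level or rise. A rise does reflect good attenders who stopped. But poor attenders remain drop-outs however active they are, and a poor attender who later stops all PA adds nothing, being counted already.

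**The two readings on the same participants** (illustration: D1 = 30%, q = 0.5, r = 10%)
- Status: 0.30 × 0.5 + 0.70 × 0.10 = 0.15 + 0.07 = 22%, a fall of 8 points.
- Ever dropped out: 0.30 + 0.70 × 0.10 = 37%, a rise of 7 points.

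One in ten good attenders has stopped in both cases, and the direction of the answer differs.

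**The case against.** The strongest reply is that the sentence opens with a comparison between groups at 9 and 21 months, and that the odds and hazard ratios also compare arms. Both follow-ups lie after the switch, so on the status reading every arm is judged by the same rule. This stands for those contrasts, and the point does not extend to them. It does not rescue the stated question: an increase after removal needs a value from before removal, and two time points that both follow it cannot supply one.

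A reader might infer something stronger: that the definitions fix the answer in advance, or that the trial could report harm from withdrawing support with no change in behaviour. The document supports neither.
- On the ever-dropped-out reading, a rise needs someone who attended well and later reports no PA at all. That is a real change. A cumulative ratio that cannot fall is also normal for an absorbing event and fits a hazard ratio.
- On the status reading, the chance of seeing a rise depends on later rates that the document does not give. Take 41 evaluable per arm (48 × 0.85 = 40.8), with independent binomial counts at T1 and later. The chance of an observed rise is 0.6% for 30% then 10%, 44% for 20% then 20%, and 80% for 30% then 40%. The Discussion's figure of more than 40% long-run non-adherence makes the last case conceivable. A large relapse would still show.

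It can also be said that the coding of drop-out over time belongs in a full protocol or analysis plan. That would answer a missing detail. Here the article itself fixes both definitions of a primary outcome and the question put to them. Finally, measures with a constant definition are already collected, and activPAL falls under the planned group-by-time models. That is true and makes the repair cheap, but the question about removing support is tied to the drop-out ratio, not to them.

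**Conclusion.** The point holds for the before-after question in the NW and SENWI arms. On the status reading, the T1-to-T2/T3 change carries a downward bias of D1·q. With D1 of 20–50% and q = 0.5 that is 10 to 25 percentage points. D1 is a proxy from the Background and q is assumed. For a given D1 above zero, the bias vanishes only if every poor attender also does no PA at all, which nothing in the document suggests. On the ever-dropped-out reading, the ratio cannot fall and combines poor attendance with stopping PA. The document does not say which reading applies, and the two can point in opposite directions.

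The defect is a bias of unknown size, not a predetermined result. The 80% versus 85% conflict, and the absence of study sessions for the control arm to attend, are separate matters; this point would remain if both were settled.

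**What to change.** Restate the question about removing support on a measure defined alike on both sides of month 3. Use the change from T1 to T2 and from T1 to T3 in the proportion inactive on SBPAAT, or in activPAL activity. Report it within the NW and SENWI arms and as the SENWI–NW difference in change. Since T1 falls when the programme has just finished, say that the T1 value is meant to describe the supported period. Report session attendance separately, as adherence to the programme.

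The cost is wording only, because both measures are already scheduled at these visits. The small downside is that the attendance-based ratio no longer enters the before-after statement.
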